### Randomization

Participants will be randomized at the individual level in a 1:1 ratio to either the AI-assisted screening group or the conventional physician-based screening group. Randomization is performed on a per-participant basis, and sample size estimation will be based on this process. DR and AMD are managed within a single unified cohort. DR and AMD can be diagnosed in the same patient, while DR and AMD are treated as separate disease-specific outcomes, and analyses will be conducted independently for each condition based on predefined eligibility criteria. Participants eligible for both conditions may contribute to both analyses.

In the conventional physician-based screening arm, fundus photographs will be interpreted by physicians without the use of any AI assistance. Physicians will review the images independently based on their clinical judgment. All physicians involved in image interpretation will receive standardized training in fundus photograph assessment prior to study initiation. In addition, a standardized reading guide will be provided to ensure consistency in image interpretation across the control group.

Randomization will be conducted using a computerized randomization module embedded within the rule engine of AIMIGS. After enrollment, each participant will be assigned a unique study ID, and allocation will be automatically generated by AIMIGS. Once the assignment is generated, the system automatically allocates each participant to the designated study arm and triggers the corresponding imaging procedures according to the predefined workflow.

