### Statistical Analysis

Baseline characteristics of the 2 study groups will be summarized as percentages for categorical variables and as means with SDs for continuous variables. Categorical variables will be compared using the chi-square test, and continuous variables will be compared using the 2-tailed *t* test. The primary analysis will follow the intention-to-screen principle, in which all randomized participants are analyzed according to their assigned study arm regardless of adherence to subsequent screening and management processes. Thus, participants will remain in the primary analysis regardless of whether AI interpretation is successfully completed, whether referral is achieved after a positive test result, or whether missing data occur within the screening workflow. These participants will still be included in the analysis of the primary outcome estimates, namely the detection rates. A per-protocol analysis will also be conducted, including only participants who adhered to the predefined study procedures, namely successful AI interpretation and, for those with positive test results, successful referral for further evaluation. Participants with any missing data during the process will be excluded from the per-protocol analysis. This population will be used to assess secondary outcome estimates, namely the PPVs. Between-group comparisons of primary and secondary outcomes will be performed using the 2 sample proportional tests.

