Although the study adopted a multicenter pragmatic design, randomization was conducted at the individual level. The AI instruments are assumed to perform consistently across different settings. Therefore, the primary analyses of the primary outcomes will be conducted as crude analyses without adjustment for potential differences in baseline characteristics or workflow processes between the study groups. Nonetheless, hospital site effects, physician-level variation, image quality, referral completion, and missing confirmatory diagnoses may have been imbalanced between groups during study execution in this pragmatic setting and could potentially confound the primary analyses. Therefore, subsidiary analyses will be conducted at both the participant and physician levels using predefined subgroup analyses to examine the consistency of screening effects across primary outcomes. These subgroups will include study site, image quality (participants with and without poor-quality images for which AI could not generate a report despite repeat testing), referral timeliness (with delayed referral defined as no referral within 2 mo), physician specialty (including family medicine and geriatric or gerontology care physicians), clinical setting (across the 4 participating hospitals), and participant-level characteristics (including age, sex, and comorbidities). These subsidiary analyses are exploratory in nature, and results will be presented descriptively without adjustment for multiple comparisons.

In addition to the originally planned 2-sample proportion comparisons in the randomized trial and subsidiary stratified analyses, post hoc multivariable regression models will be performed to account for potential clustering and confounding factors and to support the findings from the primary analyses. Site-level variability and physician-level effects will be addressed using mixed-effects models, with study site and/or physician included as random effects where appropriate. Adjustment for relevant covariates, including baseline characteristics of patients, image quality, referral completion status, and missing confirmatory diagnoses, will also be performed. Effect estimates will be reported as adjusted odds ratios with corresponding 95% CIs.

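### The crude detection-rate test is valid but forgoes a small gain; the only adjusted models are labelled post hoc and adjust for post-randomisation variables, so they cannot support it

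*Protocol article*

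**What the plan says.** All of this is in the protocol article, mainly under Statistical Analysis.

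- **Primary test.** "Between-group comparisons of primary and secondary outcomes will be performed using the 2 sample proportional tests". The section adds that "the primary analyses of the primary outcomes will be conducted as crude analyses without adjustment for potential differences in baseline characteristics".
- **Reasons given.** There are two: randomisation of individuals (the Randomization section confirms "Participants will be randomized at the individual level in a 1:1 ratio") and "The AI instruments are assumed to perform consistently across different settings".
- **Caveat.** The plan then says that "hospital site effects, physician-level variation, image quality, referral completion, and missing confirmatory diagnoses may have been imbalanced between groups" and that these factors "could potentially confound the primary analyses".
- **Response to the caveat.** Exploratory, descriptive subgroup analyses are planned by site, image quality, referral timeliness, physician specialty, age, sex and comorbidities. Regression models labelled post hoc are then added: "Site-level variability and physician-level effects will be addressed using mixed-effects models, with study site and/or physician included as random effects where appropriate". For their covariates, "Adjustment for relevant covariates, including baseline characteristics of patients, image quality, referral completion status, and missing confirmatory diagnoses, will also be performed". Results are to be adjusted odds ratios. The closing paragraphs of the section apply these models to both detection rate and PPV.
- **Outcome rule.** In the detection-rate analysis, a screen-positive participant without a confirmatory diagnosis stays in the denominator and cannot enter the numerator (Primary Outcome and Statistical Analysis).

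**The concern.** The plan names possible imbalances, keeps the primary test crude, and looks to the adjusted models for reassurance. That raises three questions.

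1. Is precision given up by ignoring baseline variables that the trial already intends to analyse?
2. Can the adjusted models do the supporting job assigned to them? They mix baseline factors with variables that arise after allocation and lie on the path from screening to detection.
3. Does consistent AI performance bear on the choice at all? Under Intervention, physicians decide on referral in both arms, with the AI output in one and without it in the other. Consistent software does not by itself make the AI effect the same for every physician.

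At stake is how a disagreement would be read. If the adjusted odds ratio came out near 1 beside a clear crude difference, a reader could conclude that confounding explained the effect, when the model had in fact adjusted the effect away.

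**Working it through.** **Step 1. Reproduce the sample size.** Inputs from Sample Size Estimation: DR 10% v 15%, AMD 5% v 10%, two-sided α 0.05, power 90%, 70% referral. Formula: n per arm = (1.960 + 1.282)² × [p1(1−p1) + p2(1−p2)] / (p2−p1)², divided by 0.70.

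- DR: variance sum 0.2175, n = 914.1, and 914.1/0.70 = 1305.9 (stated 1306).
- AMD: variance sum 0.1375, n = 577.9, and 577.9/0.70 = 825.6 (stated 825).

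**Step 2. Crude power for detection rate as defined.** Unconfirmed positives stay in the denominator, so the planned rates times 0.70 apply at full n: DR 7.0% v 10.5%, AMD 3.5% v 7.0%.

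- DR: SE = √(0.159075/1306) = 0.01104; 0.035/SE = 3.171; power = Φ(3.171 − 1.960) = 88.7%.
- AMD: SE = √(0.098875/825) = 0.01095; 0.035/SE = 3.197; power = Φ(3.197 − 1.960) = 89.2%.

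**Step 3. Gain from baseline adjustment.** SE × √(1−R²). R² is an assumption; the protocol gives none.

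| R² | DR power | AMD power |
|---|---|---|
| 0 | 88.7% | 89.2% |
| 1% | 89.0% | 89.5% |
| 5% | 90.2% | 90.7% |
| 10% | 91.7% | 92.1% |

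**Step 4. Validity of the crude test.** In simulation (2500 runs per scenario, individual 1:1 allocation, each physician in both arms, latent physician ICC 0 to 0.10), null rejection was 4.0% to 5.7%. Stratifying on physician changed the SE by about −1% to +2%.

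**Step 5. Adjusting for post-randomisation variables.**

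- *Referral completion.* Crude DR odds ratio: (0.105/0.895)/(0.070/0.930) = 1.56. Assume a PPV of 50% among completers in both arms. Completers are then 0.070/0.50 = 14% of the control arm and 0.105/0.50 = 21% of the AI arm. Among completers, detection is 50% v 50%, an odds ratio of 1.0. Among all others it is zero in both arms, so they carry no information. The adjusted odds ratio is 1.0, and the gain of 3.5 points has disappeared. Any common PPV gives the same result. If PPV differs between arms, the model returns the PPV odds ratio. This takes completion coded as confirmed attendance v everything else; the article does not give the coding.
- *Missing confirmation.* Detection is impossible when it is missing, so the logistic model has perfect separation, and those participants in effect drop out. In the same example, 70% completion leaves 0.14 × 0.30/0.70 = 6% and 0.21 × 0.30/0.70 = 9% missing. The comparison becomes 7.0/94 = 7.4% v 10.5/91 = 11.5%, an odds ratio of 1.62. The effect survives, but the intention-to-screen denominator does not.
- *Image quality.* AI Platform Functionality and the workflow legend place allocation after the photograph is taken. The quality judgement and any repeat image come after allocation, and the AI assessment exists only in the AI arm. The subgroup definition (no AI report despite repeat testing) therefore has no counterpart in the control arm.

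**Step 6. An AI effect that varies by physician.** Total SE = √(SE² + τ²/J), where τ is the SD of the risk difference between physicians and J their number. Both are assumptions.

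| J | τ | DR SE ratio, total/crude |
|---|---|---|
| 80 | 0.01 | 1.005 |
| 40 | 0.02 | 1.04 |
| 20 | 0.02 | 1.08 |
| 20 | 0.03 | 1.17 |
| 10 | 0.03 | 1.32 |

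At J = 20 and τ = 0.02 the type I error is about 6.9%. Stratifying on physician does not cure this: with 20 physicians and a log-odds slope SD of 0.3, simulated null rejection for DR was 7.6% crude and 7.2% stratified.

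**The case against.** A reader might infer from the plan's own caveat that the primary test is confounded by site or physician. The documents do not support that. Under individual randomisation such imbalance arises only by chance, and the crude SE already covers it; step 4 agrees. The plan gives individual randomisation as one of its two reasons, and that reason is sound.

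A reader might also infer that the crude SE is too small. That needs an AI effect that varies between physicians and an inference beyond the physicians taking part. The article gives neither the number of physicians nor the spread of their effects. An SD of 2 to 3 points would be 57% to 86% of the 3.5-point DR effect, so the upper end is extreme.

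Making a physician-level SE primary also has a price. With R² of 5% and physician variation together, DR power is 87.7% (40 physicians, SD 0.02) or 78.8% (20 physicians, SD 0.03), both below the crude 88.7%. This objection stands, and it is why that analysis belongs among the sensitivity analyses.

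Finally, the plan does include random effects for site and physician and subgroups by site and physician specialty. That is true. But a random intercept does not capture an effect that varies by physician, and those same models carry the post-randomisation covariates. The objection limits the point to the supporting models and a modest precision gain; it does not rescue those models.

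**Conclusion.** The crude detection-rate test is valid, and keeping it as primary would not be an error. Omitting site or physician costs about 1% of the SE at most. Baseline adjustment would add about 0.3 power points at R² of 1% and about 1.5 at 5%; both R² values are assumptions.

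The firmer finding concerns the adjusted detection-rate models. They are called post hoc although they are written down in advance, they report an odds ratio beside a comparison of proportions, and they condition on steps that determine whether a case can be detected. Under the equal-PPV illustration the whole effect vanishes. The exact loss depends on how completion is coded and on the PPV in each arm, but in no case does the model estimate the intention-to-screen effect. As written, the plan has no sound adjusted estimate of detection rate.

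Variation of the effect by physician is plausible but of unknown size. It matters for the aim, stated in the Introduction, of informing adoption across diverse clinical settings.

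**What to change.** Before phase 2 randomisation starts:

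1. Prespecify the detection-rate analysis, for DR and AMD separately, as a risk difference adjusted for hospital, age, sex and baseline comorbidity, by logistic regression with marginal standardisation. Keep the crude two-proportion test as support.
2. Remove image quality, referral completion and missing confirmatory diagnosis from every adjusted model of detection rate. Report them descriptively by arm.
3. Drop the post hoc label for models that are planned now.
4. Add a sensitivity analysis that lets the effect vary by physician: a physician-clustered SE with small-sample correction, or a physician-by-arm random effect. A physician random intercept or stratification alone does not address this. State that its interval may be wider and that it speaks to generalising beyond the participating physicians.

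The cost is a change of wording and a somewhat longer program. Site, age, sex and comorbidities are already planned as subgroup factors, so no new data are needed.

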**Figure 4. F4:**

Workflow of artificial intelligence (AI)–assisted fundus screening integrated with Picture Archiving and Communication System (PACS) and electronic health record (EHR).

The clinical workflow begins with the physician issuing an AI-assisted fundus photography order, followed by fundus photography acquisition and image upload to the PACS. The AI system then retrieves the images and triggers randomization via the AIMIGS system. In the experimental group, images undergo AI analysis, and the results are uploaded back to AI PACS. In the control arm, images are not analyzed by AI. Finally, physicians review the results in the EHR.

When a fundus image is considered insufficient for clinical interpretation, trained health care personnel will immediately reacquire the image on-site and reassess its quality. This process will not require any additional clinic visits or rescheduling. In both the AI-assisted and conventional screening arms, retinal imaging, image interpretation, and referral decisions are performed identically, ensuring that both groups follow the same care pathway at the same clinical time point. Both study arms follow an identical workflow. The only difference between groups is that the AI-assisted arm provides an additional AI-generated output to support physician decision-making, whereas the control arm relies solely on physician interpretation without AI assistance.

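### The subgroup analyses are meant to examine consistency of the AI effect, but the stated method is descriptive and names no arm-by-subgroup contrast with its uncertainty (minor, optional improvement)

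*Protocol article*

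**What the plan says.** All of this is in the Protocol article, Methods, Statistical Analysis, unless another section is named.

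- **Premise.** The crude primary analysis is introduced with "The AI instruments are assumed to perform consistently across different settings".
- **Aim.** Because site, physician and workflow factors may be imbalanced, subsidiary analyses are planned "using predefined subgroup analyses to examine the consistency of screening effects across primary outcomes".
- **Factors.** They are study site, image quality, referral timeliness, "physician specialty (including family medicine and geriatric or gerontology care physicians)", "clinical setting (across the 4 participating hospitals)", and age, sex and comorbidities. Study site and clinical setting appear to be the same factor.
- **Method.** "These subsidiary analyses are exploratory in nature, and results will be presented descriptively without adjustment for multiple comparisons".
- **Follow-on models.** Mixed-effects models take site and/or physician as random effects and add covariates. Their stated role is to deal with clustering and confounding and to support the primary result. They report adjusted odds ratios with 95% CIs. No arm-by-subgroup term and no random treatment effect is named.
- **Significance level.** A general two-sided threshold of .05 is given. Nothing links it to a judgement on consistency.

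**The concern.** The aim and the method answer different questions. Whether an effect is consistent depends on the contrast between subgroup effects and on how precisely that contrast is known. A descriptive list of stratum results gives neither. The mixed models do not fill the gap, because a random intercept for site allows the detection rate to vary between hospitals but not the effect of AI.

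At stake is what can be said about consistency at the end. If stratum results look different, a reader may infer heterogeneity where there is only sampling variation. If they look alike, the trial cannot say how much heterogeneity it has excluded. This matters modestly here, since the premise of the crude analysis is consistent performance across settings and the article hopes to inform adoption in varied settings.

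The point covers only factors fixed before randomisation: site, physician specialty, age, sex and comorbidities. Image quality and referral timeliness are outside it. The image-quality subgroup is defined as "participants with and without poor-quality images for which AI could not generate a report despite repeat testing", yet under Figure 4 the article says "In the control arm, images are not analyzed by AI", so as worded it cannot be formed in the control arm. Referral timeliness arises after randomisation.

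**Working it through.** **1. Inputs (Sample Size Estimation; Randomization).** DR 10% v 15%, 1306 per group. AMD 5% v 10%, 825 per group. Referral 70%, two-sided α .05, power .90, allocation 1:1. Number of hospitals: 4.

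**2. Reproducing the stated sample sizes.** Unpooled normal approximation, n = (p0q0 + p1q1)(1.960 + 1.282)²/(p1 − p0)², then divided by 0.70:
- DR: 0.2175 × 10.507/0.0025 = 914.1; 914.1/0.70 = 1305.9 (stated 1306).
- AMD: 0.1375 × 10.507/0.0025 = 577.9; 577.9/0.70 = 825.6 (stated 825).

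**3. Which rates to use.** The article states 10% v 15% and 5% v 10%. Under its intention-to-screen rule, screen-positives without a confirmatory diagnosis stay in the denominator as non-cases, so the observed rates could be about 0.7 times these: 7% v 10.5% and 3.5% v 7%. The reduced rates are an inference, not figures in the article. Both ends are shown.

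**4. What chance alone does when the true effect is identical everywhere.** Equal subgroups are assumed, with m per arm in each.
- SE = √[(p0q0 + p1q1)/m]; power in one subgroup = Φ(d/SE − 1.96).
- Two halves disagree on P<.05: 2p(1 − p).
- Four sites disagree: 1 − p⁴ − (1 − p)⁴.
- At least one of four reversed: 1 − [1 − Φ(−d/SE)]⁴.

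Example, DR at reduced rates: p0q0 + p1q1 = 0.1591 and d = 0.035. For halves, m = 653, SE = 0.0156, d/SE = 2.24, power 0.61. For quarters, m = 326.5, SE = 0.0221, d/SE = 1.59, power 0.35.

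| | Power, half | Halves disagree | Power, quarter | Four sites disagree | Any site reversed |
|---|---|---|---|---|---|
| DR, 7% v 10.5% | 61% | 47% | 35% | 81% | 21% |
| DR, 10% v 15% | 78% | 34% | 49% | 87% | 10% |
| AMD, 3.5% v 7% | 62% | 47% | 36% | 81% | 20% |
| AMD, 5% v 10% | 78% | 34% | 49% | 87% | 10% |

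A simulation of 100,000 trials per scenario gave the same disagreement figures. It put the chance of a zero or reversed effect in at least one of four equal sites at 23–24% (reduced rates) and 11–12% (stated rates). With assumed site shares of 40/30/20/10, sites disagreed in 82–90% of trials and at least one showed a zero or reversed effect in 19–33%.

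**5. What an interaction contrast would do.** In the same simulation, a heterogeneity test at .05 called a uniform effect inconsistent in about 5% of trials per factor. Its precision is limited. For two equal DR halves at reduced rates, SE of the difference between effects = √(2 × 0.1591/653) = 0.0221, so the 95% CI is ±1.96 × 0.0221 = ±4.3 points, against a main effect of 3.5 points.

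Power for a between-half difference as large as the main effect is Φ(0.035/0.0221 − 1.96) = 35% for DR, 36% for AMD, and 49% for either at the stated rates. For twice that difference it is 89–97%. Five independent unadjusted tests, counting comorbidities as one factor, would give at least one false positive with probability 1 − 0.95⁵ = 23%.

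**The case against.** The strongest objection is that this is an omission in a condensed article. Interaction terms and intervals for exploratory subgroups are often specified in an SAP, none is shown here, and descriptive presentation does not exclude intervals. That stands in part, and it limits the priority. But the article is not silent: it states the aim, the mode of presentation and the purpose of the follow-on models, and the stated method does not deliver the stated aim. Any SAP that includes an interaction would go beyond the article's wording.

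Three stronger readings are tempting, and the article supports none of them.

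- *Consistency will be judged by which subgroups reach P<.05.* The article does not say so. The disagreement percentages describe how easily side-by-side results can be misread. They are not error rates of a rule in the plan.
- *The crude primary analysis fails if the effect varies by hospital.* It does not. With individual 1:1 randomisation, the arm comparison estimates the average effect whether or not the effect varies. No sample size or confirmatory claim rests on the subgroups.
- *Real differences cannot be told from noise.* This is too absolute. The stated method gives no means of doing so, but a contrast with its interval could be added from the same data. Even then, power is low for moderate differences.

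It is also fair to object that an interaction test would settle little at 35–49% power. That stands, and it is a reason to report the interval rather than rely on the P value.

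**Conclusion.** The concern holds in a limited form. The article sets out to examine consistency, fixes a descriptive presentation, and names no arm-by-subgroup contrast with its uncertainty. A statement on consistency would have no quantitative support under the stated method.

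The risk of misreading is not small: about 34–47% for a two-level factor and 81–87% for four hospitals on disagreement in significance, and about 10–21% for at least one reversed hospital. These figures assume an identical true effect, equal subgroups, and either the stated rates or those rates times 0.7. The primary analysis and the sample size are unaffected. Priority: minor, optional improvement.

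**What to change.** In Statistical Analysis, for the baseline factors only (site, physician specialty, age, sex, comorbidities):

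1. Report each subgroup's arm difference in detection rate with its 95% CI.
2. Report the arm-by-subgroup interaction estimate with its 95% CI; for the four hospitals, add a 3-df heterogeneity test.
3. State that any remark on consistency rests on the interaction, not on significance within subgroups, and that a non-significant interaction is not proof of consistency.
4. Keep the exploratory label.

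The cost is one model term per factor and a sentence or two of text, with no new data. The price in interpretation is wide intervals, so any claim of consistency will be more modest.

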### Sample Size Estimation

The estimated prevalence of any DR (across stages 1-4) and AMD is 27% and 10%, respectively [29,30]. For this study, the sample size is calculated based on the assumption that 10% of patients with diabetes aged ≥20 years are diagnosed with clinically significant DR (stages 2 to 4) in the Department of Family Medicine and the Department of Geriatrics and Gerontology. Using AI-assisted diagnostic tools, the detection is assumed to increase to 15% [31].

In this real-world pragmatic setting, there was no prior evidence on the referral rates for eye disease screening in Taiwan. This study therefore assumed a referral rate of approximately 70% based on large-scale pragmatic screening trials of fecal occult blood testing and *Helicobacter pylori* stool antigen testing in Taiwan [20,21]. Accordingly, it is assumed that 70% of screen-positive individuals will be successfully referred to ophthalmologists for further examination and with a 2-tailed test, a type I error (α) of .05, and a type II error (β) of .10, the required sample size is 2612 participants (1306 per group). Approximately 870 participants are expected to be enrolled annually over an anticipated 3-year study period.

For patients aged ≥50 years in the Department of Family Medicine and the Department of Geriatrics and Gerontology in the NTUH, the prevalence of AMD is 5%, which is assumed to increase to 10% with the use of AI-assisted diagnostic tools. Assuming that 70% of the screening cases can be successfully referred to ophthalmologists and with a 2-tailed test, a type I error (α) of .05, and a type II error (β) of .10, the required sample size is 1650 participants (825 per group). Approximately 550 participants are expected to be enrolled per year.

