In addition, regarding the incomplete referral follow-up and missing confirmatory diagnoses in the pragmatic setting, the number and proportion of participants with missing outcome data will be summarized by study group, together with the reasons for missingness whenever available. The primary detection rate analysis will follow the intention-to-screen principle, in which screen-positive participants with missing confirmatory diagnosis will remain in the denominator but will not contribute to the numerator. For PPV analyses, participants with missing confirmatory diagnosis will be excluded from both the numerator and denominator. Post hoc mixed-effects regression analyses will be performed for these 2 outcomes accounting for other covariates as mentioned earlier.

A 2-sided *P* value of <.05 will be considered statistically significant. All statistical analyses will be conducted using the SAS software (version 9.4; SAS Institute).

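### Supportive models adjust the detection effect for referral completion and missing confirmation, which follow randomisation and determine the outcome

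*Protocol article*

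**What the plan says.** The primary analysis of detection is a crude two-sample comparison of proportions by intention to screen (Protocol article, Statistical Analysis). The same section then names image quality, referral completion and missing confirmatory diagnoses, beside site and physician effects, as possible confounders. It plans post hoc mixed-effects models that will support the primary findings and report adjusted odds ratios with 95% CIs. On covariates it states: "Adjustment for relevant covariates, including baseline characteristics of patients, image quality, referral completion status, and missing confirmatory diagnoses, will also be performed". The models are applied to both detection rate and PPV.

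For detection, "screen-positive participants with missing confirmatory diagnosis will remain in the denominator but will not contribute to the numerator". For PPV, participants without a confirmatory diagnosis are left out altogether.

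Two of the subgroups planned to examine consistency of the screening effect are "referral timeliness (with delayed referral defined as no referral within 2 mo") and image quality, defined as "participants with and without poor-quality images for which AI could not generate a report despite repeat testing".

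On timing, the legend of Figure 4 has randomisation triggered once the image has been uploaded, and says that control images receive no AI analysis. Under Referral After a Positive Test, referral completion and diagnosis are assessed 8 weeks after screening.

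**The concern.** A confounder must precede the allocated intervention. Referral completion and missing confirmation come after it. They also lie on the route by which AI is expected to work: the AI output informs the physician's referral decision, and a referral must be completed before a case can be confirmed. The protocol itself lists referral completion rate among its exploratory outcomes.

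These two variables also settle the outcome. A participant with no completed referral, or with no confirmatory diagnosis, cannot enter the detection numerator. In a logistic model this is quasi-complete separation: one level of the covariate holds no events, and the other holds both events and non-events.

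At stake is the reading of the trial. An adjusted odds ratio printed beside the crude result as support would answer a different question, and could disagree with a true gain in detection for reasons unrelated to confounding. These models are also the planned means of allowing for site and physician clustering, so their usefulness matters.

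**Working it through.** **Inputs from Sample Size Estimation**
- Test and error rates: "with a 2-tailed test, a type I error (α) of .05"; "a type II error (β) of .10, the required sample size is 2612 participants (1306 per group").
- Control DR rate: "10% of patients with diabetes aged ≥20 years are diagnosed with clinically significant DR (stages 2 to 4").
- AI DR rate: "the detection is assumed to increase to 15" per cent.
- Referral completion among screen-positives: 70%, applied here to both arms.
- PPV by arm: not in the document, so assumed and varied.

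**1. The plan's own figure.** With unpooled variance, n = (1.960 + 1.282)² × (0.10 × 0.90 + 0.15 × 0.85) / 0.05² = 914.15 per group (unrounded normal quantiles). Dividing by 0.70 gives 1305.9, which matches 1306. The AMD inputs (5% against 10%) give 577.9 / 0.70 = 825.6, against 825 stated. The rates are therefore read as intended.

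**2. Crude effect under the numerator rule.** DR detection is 0.70 × 10% = 7.0% in control and 0.70 × 15% = 10.5% with AI. The odds ratio is (0.105/0.895) / (0.070/0.930) = 1.56. For AMD, 3.5% against 7.0% gives (0.070/0.930) / (0.035/0.965) = 2.08.

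**3. Adjusted, coded completed or not completed.** Let s be the screen-positive share, c the completion rate and p the PPV, so detection = s × c × p. Among those not completed (including screen-negatives, who are not referred) detection is 0 in both arms, so that stratum tells the model nothing about the arm effect. Among completers the odds of detection are p/(1 − p). Hence

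adjusted OR = [p(AI)/(1 − p(AI))] / [p(control)/(1 − p(control))].

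The terms s and c drop out, although s is where AI raises detection.

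| PPV control | PPV AI | Crude OR, DR | Adjusted OR |
|---|---|---|---|
| 60% | 60% | 1.56 | 1.00 |
| 65% | 55% | 1.56 | (0.55/0.45)/(0.65/0.35) = 0.66 |
| 60% | 50% | 1.56 | (0.50/0.50)/(0.60/0.40) = 0.67 |
| 50% | 60% | 1.56 | (0.60/0.40)/(0.50/0.50) = 1.50 |

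The adjusted values are the same for AMD.

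A logistic fit to 200,000 simulated participants per arm, PPV 60% in both, gave an arm OR of 1.56 unadjusted and 1.00 with referral completion added. The referral coefficient diverged (about 32, standard error about 7400). Entering both covariates together also gave 1.00.

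In 1000 simulated DR trials per scenario at 1306 per arm, the crude test was significant in 87% to 91%. The completion-adjusted test was significant in 5% with equal PPVs of 60%. With control 60% and AI 50% it was significant against AI in 52%. With control 50% and AI 60% it was significant in 49%, in favour of AI.

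**4. Adjusted, coded only as screen-positive with missing diagnosis.** At PPV 60% in both arms, screen-positives are 0.10/0.60 = 16.7% and 0.15/0.60 = 25.0%. The missing share is 30% of these: 5.0% and 7.5%. Among everyone else the OR is [0.105/(0.925 − 0.105)] / [0.070/(0.950 − 0.070)] = 0.1280/0.0795 = 1.61. This inflates the effect slightly, because more AI-arm participants are removed as non-events.

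**5. PPV model.** Missing confirmations have already been excluded, so that covariate takes one value and its coefficient cannot be estimated.

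**6. Subgroups.** The AI-failure stratum is defined by a report that is never attempted in control, so it has no control counterpart. The stratum with no referral within 2 months has essentially no detections at the 8-week assessment, so it offers no arm comparison.

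**The case against.** The strongest reply is that nothing primary is touched. The detection test is crude and by intention to screen, the models are labelled post hoc, and the subgroups are exploratory and descriptive. That stands, and it limits the weight of the point. It does not clear the models: their covariates are already written down, and their stated role is to support the primary result.

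A reader might infer that adjustment must erase or reverse a true AI effect. The documents do not support that. They fix no coding and give no PPVs. The missing-only coding moves the OR from 1.56 to about 1.61. The Results section anticipates that AI may improve PPV, and with AI 60% against control 50% the adjusted OR of 1.50 happens to lie near the crude one. What stands is that each coding targets something other than the detection effect.

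A reader might also infer that AI image failure fixes the outcome as the other two variables do. It does not. The physician decides on referral, these participants stay in the primary analysis, and the Limitations section says uncertain cases are still referred. The fault there is the missing control counterpart. Nor is all adjustment for image quality wrong: the first image is taken before randomisation is triggered, and its quality, graded identically in both arms, could be a legitimate covariate.

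Finally, one might conclude that the crude primary test should give way to an adjusted estimate. Under 1:1 individual randomisation the crude comparison is valid, and replacing it would be a preference.

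**Conclusion.** The concern holds for the supportive analyses and should be fixed. Referral completion and missing confirmation are post-randomisation variables that set detection to zero, so calling them confounders is wrong and adjusting for them does not estimate the detection effect. Against a crude DR odds ratio of 1.56, the adjusted value ranges from 0.66 to 1.50 under completed/not-completed coding for AI-against-control PPVs between 55% against 65% and 60% against 50%. It is about 1.61 under missing-only coding at PPV 60% in both arms. These figures rest on the protocol's 10%, 15% and 70%, on equal completion in both arms, and on assumed PPVs. In the PPV model the missing-diagnosis term cannot be estimated. The AI-failure and referral-timeliness subgroups cannot show consistency of effect. The crude primary analysis is unaffected.

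**What to change.** In Statistical Analysis:

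- Delete referral completion status and missing confirmatory diagnoses from the covariate list, and stop describing them as confounders.
- Adjust only for site, physician and participant variables known before randomisation (such as age, sex and comorbidities). Keep image quality only if it is graded identically in both arms on the image taken before randomisation.
- Drop referral timeliness and AI report failure as effect-consistency subgroups. Report AI image failure descriptively within the AI arm. Referral completion is already an exploratory outcome and needs no new analysis.
- Examine missing confirmation by sensitivity analysis of the detection rate, for example multiple imputation among screen-positives, or best-case and worst-case assignment by arm.
- Keep the crude test as primary.

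The cost is protocol and analysis-plan wording. Sample size does not change and no new data are needed, unless image quality is kept, in which case a common grading of the first image must be recorded in both arms. The article describes a non-randomised pilot before the randomised phase, so the wording can be settled before randomisation begins.
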